## Abstract

Positive Youth Development (PYD) conceptualizes youth as agentic, developmentally flexible individuals whose functioning reflects dynamic person–context transactions. Rapid developments in AI now offer new opportunities to support counselors and extend intervention-based programs. The purpose of this paper is to outline an eight-week AI-supported PYD intervention for high school students and frame a feasibility-oriented mixed-method outcome research design. The model integrates daily AI micro-nudges, short voluntary micro-coaching dialogues, and one weekly 10–15-min counselor mini-session. Trait-level outcomes (self-regulation and school belonging) are assessed pre–post; state-level micro-regulation is assessed daily via Ecological Momentary Assessment (EMA). Quantitative analysis uses Lakens’s generalized within-subject effect-size formulation and baseline trend-corrected Tau-U; qualitative analysis uses deductive thematic analysis. The design is intended to demonstrate whether mechanism-consistent developmental micro-arrangements occur in naturalistic conditions rather than to test causal efficacy. This paper provides a research-ready protocol for future randomized controlled trials in AI-supported school-based intervention program.

## Introduction

Positive Youth Development (PYD) has emerged as one of the most empirically consolidated meta-frameworks in contemporary developmental research. Unlike pathology-oriented approaches that conceptualize youths primarily as carriers of vulnerability or risk, PYD advances a strength-based, asset-focused approach grounded in developmental systems thinking (Benson et al., 2006; Lerner and Callina, 2015; Waters, 2011). This framework conceptualizes adolescents as proactive and adaptable agents embedded within a complex web of intersecting systems, notably families, schools, peers, communities, and increasingly, digital environments (Fitzpatrick et al., 2017; Lerner and Callina, 2015; Potts et al., 2025). This perspective essentially transforms the central objective of youth intervention research: rather than focusing primarily on mitigating negative behaviors, the scientific target shifts toward the active cultivation of developmentally significant assets, such as competence, confidence, social connectedness, and self-regulation (de Ridder et al., 2012). These outcomes represent proactive markers of thriving rather than mere absences of pathology, necessitating intervention designs capable of detecting developmental growth rather than just clinical amelioration (Abdul Kadir and Rusyda, 2022).

While PYD offers a robust theoretical framework, its practical implementation in schools is rarely hindered by the counselor’s expertise, but rather frequently bottlenecked by structural constraints: large caseloads, fragmented schedules, limited institutional bandwidth, and the need for sustained bi-directional relational engagement (Girio-Herrera et al., 2019; Hilts et al., 2019). Despite strong theoretical consensus, a severe translational bottleneck persists in the field. Traditional PYD interventions such as manualized SEL curricula, after-school programs, and weekly counseling groups are effective but are resource-intensive, count heavily on retroactive self-reporting, and struggle with ecological validity (i.e., skills gained in a controlled classroom often fail to transfer to the unpredictable environments of the school hallways or the digital sphere). Recent studies also suggest that the effective implementation of PYD interventions frequently requires deliberate cultural tailoring (Harris and Cheney, 2015), gender-sensitive framing (Gomez-Baya et al., 2023), and multi-layered evaluation models (Eichas et al., 2010), conditions that many school counseling units struggle to operationalize on a continuous basis.

To overcome these constraints, emerging studies are increasingly turning toward digital interventions. Large-scale international trials like the European SEL4@ll program are investigating the efficacy of serious games and interactive platforms to promote and enhance social–emotional competencies outside the classroom. Methodologies like Just-In-Time Adaptive Interventions (JITAIs) and Ecological Momentary Assessment (EMA) are gaining traction (Nahum-Shani et al., 2018). These emerging approaches recognize that traditional interventions like scheduled weekly session often struggle to offer real-time responses and support, critically when a youth is experiencing a pertinent stressor or social opportunity. Recent growth in artificial intelligence (AI) and machine learning (ML) approaches in psychology and neuroscience now offers promising new possibilities for more targeted and personalized intervention in data-driven behavioral care (Benrimoh et al., 2025). AI represents the critical bridge to operationalizing these advanced, ecologically valid PYD models at scale. While early, rigid digital health tools (e.g., static applications or modules) suffered from high attrition, conversational AI scales up the automated delivery of high-frequency, low-barrier developmental affordances. Standard “one-size-fits-all” SEL curricula are not personalized to an adolescent’s specific needs and contexts, which limits adolescent engagement. By analyzing EMA data, interaction timing, and micro-choices, AI can dynamically tailor its scaffolding. For example, if an adolescent consistently reports low belonging on Tuesday, the AI can deliver customized social-connection nudges on Mondays, creating a highly personalized developmental trajectory. Adolescents experience momentary dysregulation and rapid mood shifts from peer conflict, bullying, or digital anxiety (e.g., fear of missing out). In these acute moments, AI provides immediate micro-coaching and reflective containment, guiding youth through a self-regulatory process before a situation deteriorates. Within the school setting, AI is not intended as a replacement for the counselor relationship, but as a dosage amplifier. AI can manage the high-frequency micro-interaction burden, routine tasks, and administrative oversight, thus, freeing counselors to preserve relational depth with students while significantly expanding developmental opportunities across the broader youth population.

Recent advances (e.g., Fan et al., 2025; Su et al., 2024; Zhu et al., 2024) in AI-assisted delivery systems offer novel design affordances that can alleviate counselor burden while preserving the relational core of school counseling. Micro-interaction models, such as brief reflective prompts, self-regulation nudges, or short cognitive-scaffolding dialogues, can be delivered autonomously. This may support the high-frequency dosage intended to promote developmental change without exhausting human resources (Zhu et al., 2024). The utility of AI in this context does not rely on its ability to perform deep clinical interpretation or understand adolescents accurately; rather, its value lies in delivering frequent, properly framed micro-affordances that youth can convert into meaningful developmental practice. For PYD, this matters profoundly, because PYD outcomes such as self-regulation and social connectedness are not passively absorbed classroom-style content but enacted practices requiring fresh-in-context repetition. Ultimately, counselors define the developmental arc, while AI executes the micro-dosage between relational touchpoints.

This paper addresses this methodological gap by defining an intervention design scaffold rather than reporting on clinical efficacy. Specifically, we describe an eight-week, school-embedded PYD intervention for high school students (aged 14–18) that integrates a dual-channel AI augmentation architecture: (a) daily motivational interviewing (MI)-based micro-nudges aligned with weekly developmental objectives, and (b) short, reflective micro-coaching dialogues triggered voluntarily by user or when engagement lapses. This AI architecture is anchored by a weekly synchronous 10–15-min counselor mini-session to maintain relational containment and fidelity supervision. By presenting a feasibility-oriented research blueprint rather than a commercial or finalized clinical product, this paper contributes a rigorous, research-ready protocol backbone that future randomized controlled trials can directly adapt, parameterize, and empirically test.

### Theoretical grounding and the current state of PYD

The PYD is grounded in relational developmental systems theory, which conceptualizes youth as active, flexible, and contextually embedded agents whose developmental growth emerge through dynamic, individual–environment transactions (Lerner et al., 2005). Many brain areas, particularly the prefrontal cortex, which controls complex cognition and executive functions, follow a protracted maturation period until late adolescence (Kolk and Rakic, 2022; Mahmud and Karaman, 2026). While this prolonged plasticity period increases vulnerability to environmental adversities, it also creates a developmental window during which youths are responsive to positive environmental scaffolding and capacity-building interventions. PYD rejects the historical assumption that adolescence is primarily a period of vulnerability, impulsivity, or deficit. Instead, it frames this developmental window as a period of enhanced opportunities and adaptive plasticity, where supportive ecological conditions can promote thriving rather than merely prevent dysfunction (Lerner, 2009). These conceptual foundations make PYD exceptionally well-suited for rigorous empirical outcome research, as developmental targets and outcomes are directly observable, modifiable, and measurable, rather than latent, moralistic, or aspirational.

PYD models are typically articulated in terms of multi-dimensional “assets,” such as Lerner’s “5 Cs” (Competence, Confidence, Connection, Character, Caring) (Roth and Brooks-Gunn, 2003). In recent decades, the field of PYD has shifted away from deficit-based models, which focused on mitigating adolescent risk behaviors like substance use, delinquency, and school dropout, toward strength-based, ecological frameworks. Recent theoretical advancements have expanded Lerner’s seminal “5 Cs” to include a 6th C (Contribution) and, increasingly, a 7th C (Creativity or Critical Consciousness) to address adaptive problem-solving within increasingly complex social contexts (Lerner et al., 2021; Shirzad et al., 2026). Developmental researchers now emphasize that constructs like purpose, hope, and social–emotional learning (SEL) are dynamic capacities rather than static traits, requiring continuous, real-world practice (Bowers and Bowers, 2023). Consequently, a successful transition to adulthood requires the episodic education and the continuous integration of self-regulation and social competence into the adolescent’s daily life. However, not all PYD indicators are equally sensitive to short-term intervention exposure in school settings. Broad outcomes such as “character” or “identity integration” typically emerge longitudinally (Negru-Subtirica et al., 2017), whereas regulatory processes (e.g., attention, emotion modulation, behavioral self-management) can shift proximally and repeatedly across daily school interactions (Waters, 2011; Zhang et al., 2015). For feasibility-oriented outcome designs, these regulatory constructs offer two distinct advantages: (a) they can be efficiently indexed using short Ecological Momentary Assessment (EMA) indicators, and (b) they fluctuate in real time within authentic environments. Thus, this protocol treats self-regulation not merely as an abstract trait, but as an actionable discrete set of micro-skills that the youth can practice, rehearse, and strengthen through repeated AI-driven affordances.

The second targeted PYD domain in this protocol, social connectedness, is similarly grounded in relational systems theory. During adolescence, peer significance, relational belonging, and perceived social support emerge as powerful predictors of both psychological well-being and academic engagement (Wentzel, 2017). Social connectedness is framed not as superficial “popularity” or “likability,” but as the subjective perception of being embedded in meaningful relational networks. This perception can be actively cultivated through discrete interactional shifts, such as attuning to social cues, performing micro-prosocial behaviors, or accurately decoding and interpreting peers’ emotional signals, which could be target for AI-scaffolded micro-interventions. Consequently, social connectedness serves as a synergistic secondary PYD outcome domain that is theoretically linked to regulatory practice: effectively self-regulated youth tend to interact more adaptively (Moschko et al., 2023), and these adaptive interactions, in turn, reinforce social belonging (Schlegel, 2015).

The integration of these two domains, self-regulation and social connectedness, creates a theoretically coherent, methodologically rigorous, and ecologically viable pairing for school-based implementation. Both domains have clearly defined behavioral manifestations, both exhibit sensitivity to short-term proximal dosage, and both are developmentally central for adolescents aged 14–18. Within the context of a feasibility-oriented outcome research, this dual-domain framework provides a tractable analytic target that seamlessly bridges abstract PYD theory with operationally measurable and intervention-sensitive outcomes.

By mapping specific programmatic features to Lerner’s 5 Cs, the AI is constrained and directed by established developmental theory (Bowers and Bowers, 2023; Lerner et al., 2005). It does not operate as an open-ended conversational agent, but as a highly targeted developmental scaffold (Fan et al., 2025). Each micro-nudge and coaching dialogue is mathematically weighted to prompt behaviors that actively build Competence, Confidence, Connection, Character, or Caring. Consequently, the technology serves as a precision instrument to operationalize the exact individual-environment transactions that relational developmental systems theory identifies as the engine of youth thriving (Lerner and Callina, 2015; Su et al., 2024).

### Model definition

The model is conceptualized as a developmental delivery architecture wherein human counselors establish the relational frame and developmental arc, while AI system executes the high-frequency micro-dosage required for proximal skill enactment. Critically, this intervention does not conceptualize AI as a counselor analog, therapist substitute, or diagnostic component, but as a systemic dosage amplifier. Counselors maintain primary responsibility for relational containment, while the AI autonomously delivers the high-volume, micro–developmental practice opportunities that human counselors cannot feasibly scale. This approach is grounded in the developmental reality that self-regulation and social connectedness are not cultivated through episodic learning, but through continuous, real-world repetition. The architecture therefore mirrors the mechanisms of motor-skill acquisition: micro-practice → consolidation → transfer. This counselor–AI co-delivery framework makes this repetition feasible within standard school constraints.

The intervention is deployed throughout eight consecutive school weeks. Each week focuses on one thematic developmental objective (see Table 1) and offers a synchronous 10–15-min counselor mini-session. This mini session serves as a vital “anchor point,” grounding the week’s developmental target in a supportive relational context while allowing the counselor to check ecological fit, safety, and progress. The remainder of the weekly dosage is delivered digitally through daily MI-style micro-nudges (e.g., ≤ 40 words). The sequence is intentionally graded to build capacity over time: initial weeks emphasize foundational awareness and micro-choice recognition; intermediate weeks prioritize active skill application in real-life contexts; final weeks focus on value mapping, identity congruence, and future transfer. In essence, the intervention is paced not by superficial “topic rotation,” but through the cumulative scaffolding of practice complexity.

**Table 1 tab1:** Structured eight-week progression of developmental objectives and measurable indicators.

Week	Theme	Weekly skill focus	Measurable outcome wording	Measurement schedule
0				Weeks −2 to −1: Consent, demographics, BSCS/SSBS (pre), two-week daily EMA baseline (Phase A)
1	Awareness	Noticing internal states & situational triggers	Student(s) can label at least one emotional state + one situational trigger per day	
2	Micro-Choices	Identifying ‘choice points’ in daily routines	Student(s) can describe one moment/day where a micro-choice was made intentionally	
3	Regulation Moves	Using micro-regulation strategies in real time	Student(s) can report using at least one regulation move during a difficult moment	
4	Social Signals	Reading emotional/social cues in peers	Student(s) can identify one social cue observed in a peer interaction per day	Weeks 1–8: Daily EMA, weekly mini-session, fidelity log
5	Connection Behaviors	Performing pro-social action steps	Student(s) can report one specific pro-social action per day	
6	Real-World Practice	Applying skills in naturalistic school contexts	Student(s) can name one applied skill used in a school scenario that occurred	
7	Integration & Identity	Linking skills to values and identity	Student(s) can articulate one personal value and how a behavior reflected it	Week 8: BSCS/SSBS (post)
8	Transfer & Future Self	Projecting skills into future-oriented plans	Student(s) can describe one future scenario where learned skills will be used	

The AI augmentation is delivered through two channels. Channel 1 deploys daily micro-nudges aligned with the overarching weekly objective; these function as single-turn reflective invitations that increase the density of developmental prompts across the student’s daily ecological environment. Channel 2 consists of short-form (3–5 turn) micro-coaching dialogues, triggered either by voluntarily user initiation or automatically triggered following a 24-h lapse in engagement. Both channels are strictly reflective, offering no directive advice, clinical instruction, or evaluative feedback. The goal is to systematically increase the frequency with which the student monitors internal states, detects micro-choice moments, decodes social signals, and reflects on prosocial behaviors. Over the 8 weeks, this dual-channel architecture aims to expose the student to dozens of micro self-regulation enactments and relational affordances that incrementally accumulate to drive sustained and measurable developmental change.

In this intervention, the counselor supervises fidelity, not content generation. The synchronous weekly mini session(s) serves to anchor and facilitate relational connection, provide developmental interpretation, and maintain clinical boundaries. To support this, counselors receive an auto-generated weekly summary of the student’s (a) micro-nudge delivery and engagement, (b) micro-coaching activity, and (c) reflective note submissions. The counselor’s task is not to manually “grade” or “correct” but to contextualize the AI-facilitated micro-work within the student’s authentic relational ecology, and to intervene if emotional distress or dysregulation emerges. Ultimately, this design upholds the core ethical framework that the AI augments the intervention dosage, but human counselors remain fundamental anchors of the developmental and relational process.

## Method

### Setting and participants

The intervention is designed for implementationwithin mainstream high school counseling settings serving adolescents aged 14–18. This ecological frame is intentional. As a feasibility study, the sample size is determined by the need to evaluate implementation applicability and estimation precision rather than statistical power for clinical efficacy. A target sample of 40–60 students from routine school caseloads, is sufficient to yield narrow confidence intervals (CIs) for recruitment/retention/compliance and to visualize heterogeneous individual-level micro-trajectories within an authentic delivery context. Feasibility will be evaluated against four pre-specified operational thresholds: (a) a recruitment rate ≥ 70% of eligible students; (b) a retention rate of ≥ 80% (defined as completing both pre- and post-intervention trait measures); (c) a median EMA compliance of ≥ 60% for daily prompts (1–7 Likert scale) across Weeks 1–8; (d) an intervention fidelity of ≥ 75% (defined as weeks where all three checklist items are met). These thresholds were derived from established benchmarks in the feasibility and pilot trial literature (Billingham et al., 2013; Eldridge et al., 2016). The 70% recruitment and 80% retention rates are widely adopted as minimum indicators of a viable study pipeline for a subsequent full-scale trial. The 60% EMA compliance threshold reflects the empirically observed lower bound of acceptable ecological momentary data completeness in adolescent digital health studies (Shiffman et al., 2008); compliance below this level produces phase lengths insufficient for reliable Tau-U estimation. The 75% fidelity threshold is grounded in the intervention science literature’s recommendation that at least three-quarters of protocol sessions be delivered as specified before efficacy conclusions can be considered (Bellg et al., 2004). Together, these benchmarks ensure that a positive feasibility verdict is substantively meaningful rather than nominally so.

Participation is voluntary, contingent upon the student’s willingness to engage in daily reflective micro-interactions for 8 weeks. Inclusion criteria are intentionally minimal to maximize ecological validity: must (a) possess sufficient functional literacy to interpret daily reflective prompts, (b) have access to a digital interface (e.g., mobile device), and (c) be available for one weekly 10–15 min synchronous mini-session with a counselor. Exclusion criteria are guided by safety and feasibility logic rather than clinical diagnostics. Students presenting with acute crisis indicators (e.g., active suicidal intent, imminent risk of harm, or major protective disclosure) are not enrolled into this model because such circumstances require immediate professional care with crisis protocols. The purpose of this design is not to triage or treat acute dysregulation but to examine whether an AI-supported PYD scaffold can be realistically implemented within an ordinary school setting.

To ensure participant safety, any Adverse Events (AEs) including disclosures of harm, acute distress, or technology misuse will be monitored, documented, and reported to the responsible researcher within 24 h. AEs trigger immediate counselor escalation in accordance with institutional safeguarding policies; serious AEs are logged and reviewed by the school’s safeguarding lead. The AI system is structurally restricted from issuing behavioral directives; all guidance remains purely reflective and strictly under human counselor’s clinical oversight.

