Quantitatively, the design combines a within-subject trait-level pre–post comparison with an embedded single-case AB probe. The sequence consists of a pre-intervention baseline (Phase A; Weeks −2 and −1) and an active intervention period (Phase B; Weeks 1–8). The two-week baseline was adopted. A minimum of 10 data points in Phase A provides a more stable trend estimate for Tau-U baseline correction and more clearly distinguishes pre-existing directional drift from intervention-related change. Throughout Phase B, state-level EMA micro-ratings (1–7 Likert scales) index continuously index momentary regulation states. Trait-level self-regulation and social connectedness are measured at pre- and post-intervention timepoints via the within-subject standardized mean difference (Cohen’s *d*). To rigorously capture the dynamics of the state-level micro-trajectories, data will be evaluated using Tau-U, a robust, best-practice non-overlap effect size optimized for AB sequences in single-case experimental design (SCED) methodology.

The qualitative strand consists of (a) weekly counselor fidelity logs and (b) brief, one-sentence reflective student notes. These materials are not narrative interviews; rather, they serve as real-time process-evidence. Therefore, the analytic objective is not to achieve thematic saturation, but to execute mechanism-alignment detection. Reflexive thematic analysis will be used to identify and verify whether developmental practice indicators outlined in Table 1 occurred within a real-world educational environment.

All reflective notes remain accessible to the counselor to preserve the core ethical principle of human relational containment. The AI system does not store raw text beyond the generation of summary logs. Data retention adheres strictly minimal-retention feasibility norms; export functions are disabled. No participant data or conversational data is used for model training or model improvement. Furthermore, no algorithmic action is permitted without the possibility of immediate human override; should emotional dysregulation signals emerge, counselors escalate the case in accordance with established institutional safeguarding protocols. In this design, the AI is never the locus of clinical decision; rather, it is the engine for prompt density. Human counselors retain absolute safeguarding authority and interpretive control.

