#### Missing data handling

Missing data for the trait outcomes (BSCS, SSBS), analyses will be managed via pairwise availability with sensitivity checks using last-observation-carried-forward for descriptive ranges. For the state-levelEMA data, missing days will simply be omitted because Tau-U inherently tolerates unequal phase lengths and missing data points within time-series sequences. To rigorously assess the effect of intervention dosage, per-participant compliance (percentage of EMA prompts answered) will be reported and descriptive contrasts comparing high- compliance (≥ 60%) versus low- compliance (< 60%) will be conducted.

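### EMA criterion (c) is decided on the sample median, but one of its two stated reasons is a minimum for each student's Tau-U series, so it can be met with about half the students below that minimum

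*Protocol article*

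**What the plan says.** Under Setting and participants, the protocol article sets four operational thresholds for feasibility. The third is "a median EMA compliance of ≥ 60% for daily prompts (1–7 Likert scale) across Weeks 1–8". Two reasons for the 60% figure follow. The first is a benchmark: "The 60% EMA compliance threshold reflects the empirically observed lower bound of acceptable ecological momentary data completeness in adolescent digital health studies". The second is analytic: "compliance below this level produces phase lengths insufficient for reliable Tau-U estimation". The section closes by saying that the four benchmarks together make a positive verdict meaningful in substance and not just in name.

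Under Research design, "the design combines a within-subject trait-level pre–post comparison with an embedded single-case AB probe", and Tau-U is the effect size for the AB sequences.

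Under Missing data handling, the unit is the student: "per-participant compliance (percentage of EMA prompts answered) will be reported". The 60% figure returns there as a cut between students, for description only: "descriptive contrasts comparing high- compliance (≥ 60%) versus low- compliance (< 60%) will be conducted". The same section also says of the EMA series that "missing days will simply be omitted because Tau-U inherently tolerates unequal phase lengths and missing data points within time-series sequences".

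**The concern.** The rule and one of its reasons refer to different units. A phase length belongs to one student's series, so a statement that compliance under 60% makes phases too short for Tau-U is a statement about each student. A median of at least 60% says only that about half the students reach that level. It does not respond to how many of the remainder fall short, up to about half, or to how far short they fall.

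This matters because (c) is the only one of the four thresholds that counts EMA responses. Retention is defined by completing the pre and post trait measures. Fidelity is defined by nudges opened, notes submitted and behaviors described. The state-level Tau-U results are one of the three evidence streams in the triangulation matrix. A positive verdict could therefore be declared while a large minority of the series are, by the article's own stated standard, too short to analyze reliably.

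**Working it through.** The 60% figure is a cited benchmark, not a calculated one, so there is no figure of the plan's own to reproduce. The check is what a median rule at 60% does and does not guarantee.

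**Inputs from the protocol article**
- Sample: "A target sample of 40–60 students from routine school caseloads" (Setting and participants).
- Rule: median compliance of at least 60% over Weeks 1–8 (same section).
- Unit of compliance: the participant (Missing data handling).
- Phase B: eight weeks (Research design).

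**Assumptions**
- The median is taken over students. The article does not say so, but it is the natural reading given per-participant compliance.
- Students are independent, and each has the same probability q of being below 60%. The documents give no value for q, so a range is shown.

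**Step 1: how many students may be below 60%?** With n even, the sample median is the average of the two middle values. Let X be the number of students below 60%.
- If X ≤ n/2 − 1, both middle values are at least 60%, so (c) is met whatever the low values are. The limit is 19 of 40 (47.5%), 24 of 50 (48.0%) or 29 of 60 (48.3%).
- If X = n/2, (c) is met only when the two middle values average at least 60%, for example 59% and 61%. The limit is then exactly half: 20 of 40, 25 of 50 or 30 of 60.
- With n odd, the limit is (n − 1)/2: 20 of 41 (48.8%) or 29 of 59 (49.2%).

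**Step 2: how often is (c) met?** With X ~ Binomial(n, q), the probability that (c) is met lies between P(X ≤ n/2 − 1) and P(X ≤ n/2). The interval reflects the tie at X = n/2.

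| True share below 60% (q) | n = 40 | n = 50 | n = 60 |
|---|---|---|---|
| 0.40 | 0.870–0.926 | 0.902–0.943 | 0.925–0.956 |
| 0.45 | 0.684–0.787 | 0.716–0.803 | 0.742–0.818 |
| 0.50 | 0.437–0.563 | 0.444–0.556 | 0.449–0.551 |

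The lower bounds hold however far below 60% the low group lies. They are for (c) alone, not for the four thresholds jointly.

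**Step 3: what does falling below 60% mean for a series?** The article does not fix the number of prompt days.
- With 56 calendar-day prompts in Phase B, 60% is 0.60 × 56 = 33.6, so a student just below 60% has 33 points.
- With 40 school-day prompts, 60% is 0.60 × 40 = 24, so such a student has 23 points.

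Whether 23 or 33 points are too few is exactly where the article disagrees with itself. Setting and participants says that phases become too short below 60%. Missing data handling says that Tau-U tolerates missing points and unequal phases.

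**Step 4: what would a share-based rule do?** The required share is illustrative only, because the documents give none. The rule is met when X does not exceed the number allowed below.

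| Required share at ≥ 60% | Allowed below (n = 40 / 60) | P(met), q = 0.40 | P(met), q = 0.20 | P(met), q = 0.10 |
|---|---|---|---|---|
| 70% | 12 / 18 | 0.129 / 0.072 | 0.957 / 0.978 | >0.999 / >0.999 |
| 80% | 8 / 12 | 0.006 / 0.001 | 0.593 / 0.576 | 0.985 / 0.994 |

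Either share separates a sample with 40% of students below from one with 10% below, where the median rule does not. The 80% share is demanding: it is met only about 58–59% of the time when exactly 20% are below.

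**The case against.** The best reply is that Tau-U is not the only reason for 60%. The first reason is a benchmark for data completeness, and a sample summary such as the median can serve that purpose. This stands: the mismatch is with one of two reasons, not with the whole basis of the threshold.

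It can also be said that the weak part is the Tau-U clause and not the median. A student just under 60% may still have 23 or 33 Phase B points, and the missing-data section treats gaps as tolerable. This stands too, and it is why removing that clause is an acceptable alternative. It does not help the text as written, which asserts both things.

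A third reply is that per-participant compliance and the split at 60% would let any reader see the low group. They would, but only descriptively; the share does not decide the verdict.

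Three stronger readings are tempting, and the documents do not support them.
- A reader might infer that the plan would accept a sample in which nearly half the students never answer. At n = 40, 19 students at 0% and 21 at 60% do give a median of 60% and a mean of (19 × 0 + 21 × 60)/40 = 31.5%. That is a constructed extreme. The thresholds are applied together, and students so disengaged would probably also pull down retention or fidelity, although neither counts EMA responses.
- A reader might infer that low-compliance students are wrongly kept in the Tau-U analysis. The article states no minimum series length, but that detail is commonly left to a full protocol or analysis plan, which is not shown.
- A reader might infer that 80% is the right share because retention uses it. Retention is defined on two trait assessments and gives no basis for an EMA share.

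**Conclusion.** The concern holds in a limited form. One of the two reasons given for the 60% threshold applies student by student, while the criterion is decided on the sample median, so meeting it does not deliver what that reason asks for. It can be met with up to about half the students below the level called insufficient. When 40% are truly below, (c) alone is met with probability at least 0.870 (n = 40), 0.902 (n = 50) and 0.925 (n = 60).

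These figures assume a median over students, independence between students and a common q. They count a student at 59% and one at 0% alike as below. They say nothing about the joint probability of meeting all four thresholds.

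This should be settled before data collection, because it changes what a positive feasibility verdict can be taken to show. It does not make the median an improper summary of compliance. The two statements on Tau-U and missing points also need to be reconciled.

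**What to change.** Preferred: restate criterion (c) as the proportion of enrolled students who answer at least 60% of daily prompts in Weeks 1–8, reported with a 95% CI. The sponsor should pre-specify the required share and justify it; 70–80% is an illustration, not a figure from the documents. Keep the median as a descriptive summary.

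Alternative: keep the median as the criterion, delete the Tau-U reason, rest the 60% on the completeness benchmark alone, and state that meeting (c) shows only that about half the students reach 60%.

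Under either option, bring the Tau-U wording in Setting and participants into line with that in Missing data handling.

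Cost: about one sentence for the criterion, plus that wording. No new data are needed, since per-participant compliance is already to be reported. The downside of the preferred option is a stricter criterion that may be met less often.
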